#### 4.4 Exclusion criteria (study baseline)

- Any serious unstable medical condition at study baseline
- Any criteria that in the opinion of the investigator indicate that the patient is unable to participate in the full study.

#### 4.5 Randomisation criteria (month 6)

- Completion of six months of continuous first-line ART.
- For ART Naïve patients: A VL of <1000 copies/mL at the first VL measurement after initiation at month 6 of ART or a VL of >1000 copies/mL at month 6 of ART followed by a VL of <1000 copies/mL before or at month 9 of ART.
- Absence of severe active opportunistic infection requiring therapy at time point of randomisation, excluding infection with *M. tuberculosis*.

## 5 DESIGN & METHODS

### 5.1 Study design

#### 5.1.1 Inclusion, observational follow-up & randomisation (baseline to month 6 of ART)

Eligible patients attending Ndlovu Medical Centre will be recruited as described under “6.2.2 Recruitment procedure” and “6.2.5 Informed consent”. A subgroup of patients is enrolled prior to start of ART in order to collect baseline plasma samples and data on potential risk factors for therapy failure. These patients will receive observational study follow-up visits at month 3 and month 6 after start of ART. In standard of care, at month 6 of ART a VL measurement is performed to determine initial treatment success, indicated by suppression of the VL to <1000 copies HIV-1 RNA/ml. To ensure that only patients with initial treatment success are selected for randomisation, randomisation will be performed after availability of the month 6 VL into either the control arm or intervention arm. (described under “7.2.4 Randomisation procedure”). In addition, a group of patients already on ART and with a last annual VL result of <1000 copies/ml obtained <6 months previously will be enrolled, and will be followed observationally until 6 months after the last viral load, at which point these patients will be randomised in the same fashion. After randomisation, patients in both study arms will return for study follow-up visits on a three-monthly basis, at month 9, 12, 15, 18, 21 and 24 after start of ART or after the last VL measurement. In addition, patients will be called back for additional study visits (max. 2) in case of a detected VL >1000 copies/ml during any of these visits. All visits in both arms, including aforementioned additional call back visits will coincide with standard of care medication collection visits to the clinic. In case of a switch to second-line therapy, patients in both arms will continue three-monthly follow-up visits in an observational manner, and guidelines for monitoring of second-line therapy are followed.

#### 5.1.2 Control arm follow-up – standard of care HIV treatment monitoring

300 patients randomly assigned to this arm will be monitored in full concordance with current South African NDoH guidelines in use at the study site. Viral load measurements will be performed at month 12 and 24 after start of ART (for newly initiated patients) or at month 12 and 24 after the last VL measurement (patients already on ART). If a VL >1000 copies/ml is detected, the patient is called back for counselling for therapy adherence and repeat VL measurement, 2 months after the initial VL measurement. If the repeat VL measurement is >1000 copies/ml after adherence counselling, this is taken to be indicative of therapy failure due to development of drug resistance and a switch to second line therapy is made, together with intensified adherence counselling, without verifying the cause of virological failure by

performing DLM or drug resistance testing. If VL drops to <1000 copies/ml after adherence counselling, the first line treatment is maintained. For a full overview of study visits and clinical algorithms in the control arm, see Figure 1: ITREMA study flowchart.

Sample collection in the control arm consists of storage of EDTA-derived plasma and a DBS at study baseline and at the subsequent study visits at month 3, 6, 9, 12, 15, 18, 21 and 24 of ART, as well as during any additional study follow-up visits in case of a VL >1000 copies/ml. Blood draws at baseline, month 3, 6, 12 and 24 after start of ART, and in case of follow-up after a VL >1000 copies/ml coincide with blood draws performed as part of standard of care. The following measurements will be performed on stored samples:

- An additional CD4 measurement at study month 6, in order to assess eligibility for randomisation and rate of CD4-count recovery.
- Retrospective VL testing on stored EDTA-derived plasma in case of clinical therapy failure, in order to retrospectively examine the duration of viremia.
- Retrospective drug resistance testing on stored DBS in case of clinical therapy failure to examine the accumulation of resistance mutations over time.
- Screening for transmitted drug resistance by drug resistance testing on stored DBS obtained as at baseline, prior to start of ART.

### 5.1.3 Intervention arm follow-up – Intensified HIV treatment monitoring

300 patients randomly assigned to this arm will be monitored using the investigational intensified monitoring strategy. This strategy consists of 3-monthly VL monitoring at month 9, 12, 15, 18, 21 and 24 (after start of ART in initiating patients or after the last VL measurement in patients on ART). If a VL measurement > 1000 copies/mL is detected, the patient will be called back for a follow-up study visit at the next monthly medication collection visit (4 weeks after detection of elevated VL). Upon arrival DLM is performed, the VL measurement is repeated, and a DBS prepared and stored at room temperature. Procedures following this depend on the result of DLM:

- If drug levels are detected by DLM, the result of the VL measurement is awaited. If the repeat VL is >1000 copies/ml, the DBS is shipped directly by courier to the WHO reference laboratory for drug resistance testing. The reference laboratory will provide feedback by means of a digital resistance report to the coordinating research physician. The patient will be called back for a second follow-up study visit at the next monthly medication visit (8 weeks after detection of elevated VL), either for prescription of second-line therapy or continuation of first-line therapy, guided by the

result of resistance testing.

- If DLM at the first follow-up visit indicates that drug levels are not detected, intensified counselling is performed at the same visit and first-line therapy will be maintained, regardless of the result of the repeat VL measurement. The patient will not be called back and the next VL will be performed at the next scheduled three-monthly time point. However, if the VL result at this visit is again >1000 copies/ml, drug resistance testing will be performed regardless of the outcome of DLM.

For a full overview of study visits and clinical algorithms in the control arm, see Figure 1: ITREMA study flowchart.

Sample collection in the control arm consists of storage of EDTA-derived plasma and a DBS at study baseline and at the subsequent study visits at month 3, 6, 9, 12, 15, 18, 21 and 24 of ART, as well as during any additional study follow-up visits in case of a VL >1000 copies/ml. Blood draws at baseline, month 3, 6, 12 and 24 after start of ART, and in case of follow-up after a VL >1000 copies/ml coincide with blood draws performed as part of standard of care. The following measurements will be performed on stored samples:

- An additional CD4 measurement at study month 6, in order to assess eligibility for randomisation and rate of CD4-count recovery
- Retrospective drug resistance testing on stored DBS in case of clinical therapy failure to examine the accumulation of resistance mutations over time.
- Screening for transmitted drug resistance by drug resistance testing on stored DBS obtained as at baseline, prior to start of ART.

Figure 1a: ITREMA study flowchart – enrolment to randomisation

[figure not shown]

Figure 1b: ITREMA study flowchart – post randomisation

[figure not shown]

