## **Study outcomes**

### **Virological effects of intensified monitoring**

- Amount of drug resistance mutations per patient with therapy failure in each arm
- Selection of specific resistance mutations associated with multi-drug resistance in each arm
- Consequential loss of therapeutic options between arms
- Rate of virological failure in the absence of drug resistance between arms
- Rate of resuppression after detectable viremia in each arm
- Unnecessary treatment switches averted in the intervention arm and unnecessary therapy switches made in the control arm

- Loss of therapeutic options over time in the presence of a failing regimen in both arms
- The influence of genotypic resistance testing on the choice for a second line regimen in the intervention arm
- Time on a failing regimen per patient with therapy failure in each arm

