It is expected that intensified VL monitoring will detect therapy failure at an early stage, prior to selection of multiple resistance mutations. In those patients in which viremia is present, DLM is expected to identify patients with (nearly) undetectable plasma drug levels due to major non-adherence, in which the risk of drug resistance is expected to be lower. This will enable clinicians to provide intensified and tailored adherence counselling and prevent unnecessary resistance testing. Effective intensified adherence counselling has the potential to resuppress the VL to below 1000 copies/ml in over half of cases, if performed in an effective manner and in a setting of frequent VL monitoring.

When non-adherence is not detected by DLM, quick follow-up drug resistance testing will detect drug resistance prior to accumulation of resistance mutations and assure safe options for future treatment, preventing the use of more toxic regimens and therefore avoiding additional morbidity. It will also identify those patients in whom drug resistance mutations are absent, thus avoiding unnecessary treatment changes. Finally, as intensified monitoring is expected to reduce the duration of viremia during therapy failure it is expected to lower HIV transmission rates and transmission of drug-resistant HIV. Although the costs of intensified monitoring itself are higher, implementation of the strategy may be cost-effective or even cost saving by preventing unnecessary second-line therapy, reducing patient morbidity and mortality and reducing transmission rates.

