#### 5.2.4 Follow-up of elevated viral load measurement

##### 5.2.4.1 Intervention arm

In case of a VL >1000 copies/ml of a patient in the intervention arm, feedback of this result will be given by the clinical site laboratory after 2-5 working days). The patient will be notified to report back to the research clinician or nurse at his/her next monthly routine clinical visit for medication collection (day 28 after study visit). At this visit repeat viral load testing, DLM and collection of plasma and DBS is performed. If DLM indicates no detectable drug level (see “5.2.5 Drug Level Monitoring”), the patient is informed of this result, and intensified adherence counselling is performed. If DLM does not indicate non-adherence, standard of care adherence counselling will be performed. The result of the second VL will be available after 2-5 working days (day 31-33 after study visit). In case of a second VL >1000 copies/mL and a detectable drug level at DLM, the DBS will be sent to the WHO reference laboratory for drug resistance testing and patients will be notified again to report back to the research clinician or nurse at his/her next monthly routine clinical visit (day 56 after study visit) for genotype guided switch to second-line therapy or for genotype guided continuation of treatment combined with counselling in case no relevant resistance is detected. In case DLM detected no drug level, the DBS is not sent and genotyping not performed. The patient will not be called back and not be switched to second-line therapy prior to the next study visit. In case an elevated VL is again detected at the subsequent study visit (day 84 after previous study visit), a DBS is sent directly for drug resistance testing and genotype guided therapy switch or continuation is performed. In case of continuation, the three monthly monitoring frequency is maintained. In case of switch, a VL will be performed six months after the switch to evaluate initial therapy success. Three monthly study visits will be continued in an observational manner, at which storage of DBS and plasma is performed.

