#### 5.2.6 Dried Blood Spot-based Drug Resistance Testing

In case of a confirmed detectable viral load (>1000 copies/ml) in the presence of detectable drug level as indicated by DLM, a dried blood spot (DBS) sample acquired during the second viral load measurement will be sent to a WHO reference laboratory for drug resistance testing, where genotypic HIV-1 drug resistance testing will be performed using an RT-only assay optimized for non-B HIV subtypes. This assay has been validated for use on DBS and implemented in a pilot study at Ndlovu Medical Centre. The assay consists of a single-round one-tube RT-PCR to amplify the viral RT-gene between codons 40-238, followed by population sequencing of the amplified fragment in both directions using 2 primers only. With this approach all RT resistance information relevant to first-line regimens is generated at minimal cost for laboratory reagents, equipment and personnel. If resistance testing is indicated in patients using second line therapy, a protease-only genotypic assay will be performed on the DBS in addition to the RT-only assay. Drug resistance testing will also be performed retrospectively on stored DBS in all patients with therapy failure in the control group, using the same approach as described above. The WHO reference laboratory will provide the treating physician with the result and interpretation of the drug resistance test, containing viral subtype, a list of all mutations, specific indication of relevance of these mutations to drug-resistance, a drug susceptibility ranking using resistance interpretation algorithms, and an overall interpretation with treatment advice taking local availability of antiretroviral drugs into account.

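### The protocol contradicts itself on retrospective genotyping of intervention-arm failures; following section 5.2.6 would leave informative gaps in the resistance outcomes

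*Protocol*

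**What the plan says.** Four parts of the Protocol bear on who is genotyped for the outcome analysis.

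- **Section 5.1.3 (intervention arm).** The sample paragraph reads "Sample collection in the control arm consists of storage of EDTA-derived plasma and a DBS", although the heading is the intervention arm. Its list of tests on stored samples includes "Retrospective drug resistance testing on stored DBS in case of clinical therapy failure to examine the accumulation of resistance mutations over time".
- **Section 5.2.6 (resistance testing).** In real time, a DBS is genotyped when the raised viral load (VL) is confirmed and drug is detectable. The section then adds: "Drug resistance testing will also be performed retrospectively on stored DBS in all patients with therapy failure in the control group". It has no matching sentence for the intervention arm.
- **Section 5.2.4.1 (intervention arm, raised VL).** "In case DLM detected no drug level, the DBS is not sent and genotyping not performed". Section 5.3.1.5 repeats this. Sections 5.1.3 and 5.2.4.1 add an exception: if the VL is again above 1000 at the next three-monthly visit, resistance testing is done whatever the drug level.
- **Outcomes.** The Summary lists first, among the virological outcomes, "Amount of drug resistance mutations per patient with therapy failure in each arm". Section 6.1 adds K65R or more than one NNRTI mutation. It counts an averted unnecessary switch in the intervention arm as two successive raised VLs without resistance mutations.

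Table 4 shows DBS storage at every viraemia visit, including the column for two raised VLs with no drug detected.

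**The concern.** The resistance outcomes compare mutations among patients with failure in each arm. That comparison needs genotypes obtained by the same rule in both arms. If 5.2.6 is the working instruction, control patients with two VLs above 1000 are genotyped regardless of drug level. Intervention patients with two VLs above 1000 and no detectable drug are not, if they then resuppress, are lost, or have no later study visit (viraemia first found at month 24).

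These patients are not a random subset. Section 2.2 describes those with undetectable drug as patients "in which the risk of drug resistance is expected to be lower". Dropping them would raise the apparent resistance rate in the intervention arm; counting them as resistance-free would tend to lower it. The averted-switch outcome in 6.1 has no drug-level condition, so it cannot be scored for them at all without a genotype.

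**Working it through.** **1. The passages side by side**

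| Patient with two VLs above 1000 | If 5.2.6 governs | If 5.1.3 is read as meaning the intervention arm |
|---|---|---|
| Control | Genotyped retrospectively | Same |
| Intervention, drug detected | Genotyped in real time | Same |
| Intervention, no drug detected, still above 1000 at next visit | Genotyped then | Same |
| Intervention, no drug detected, resuppressed, lost or no later visit | No genotype | Genotyped only if this course counts as clinical therapy failure |

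The last row is the whole issue. Section 5.1.3 does not say whether that course counts as clinical therapy failure. It keeps the patient on first-line treatment whatever the repeat VL shows. In 5.1.2, by contrast, a second raised VL is itself taken as failure.

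**2. The plan's own figures**

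Section 6.7.3 takes K65R prevalence among failures as 70% and 17%. With two-sided alpha 0.05, power 0.90 and unpooled variances:

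(1.960 + 1.282)² × (0.70×0.30 + 0.17×0.83) / 0.53² = 10.51 × 0.3511 / 0.2809 = 13.1, so 14 failures per arm, as stated. The printed error labels look transposed, but taken literally (two-sided alpha 0.10, power 0.95) they give 13.5, also 14.

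Inflation: 14 / 0.20 / 0.85 = 82.4, so 83 per arm, as stated (10% loss a year over 18 months = 15%).

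On the same rates, 300 randomised per arm gives 300 × 0.85 × 0.20 = 51 failures. The 20% is cumulative VL above 1000, so the number with two raised VLs may be smaller.

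**3. Illustration of the distortion in K65R**

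The documents give neither the ungenotyped share *s* nor the K65R prevalence *q* among those patients. Assume *s* = 10–30% (5 to 15 of 51) and a true intervention rate of 17%.

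- Patients dropped: apparent rate = (0.17 − *s*·*q*) / (1 − *s*)
- Patients counted as negative: apparent rate = 0.17 − *s*·*q*

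| Handling | *q* | *s* = 10% | *s* = 30% |
|---|---|---|---|
| Dropped | 0 | 0.17/0.9 = 18.9% | 0.17/0.7 = 24.3% |
| Dropped | 17% | 17.0% | 17.0% |
| Counted as negative | 17% | 0.17×0.9 = 15.3% | 0.17×0.7 = 11.9% |

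Against a control rate of 70%, the true difference of 53 points would appear as 51.1 or 45.7 points in the first row and as 54.7 or 58.1 points in the last. With 51 control failures, power stays at 0.99 or above for *s* up to 30%. The issue is bias, not power.

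**The case against.** The strongest reply is that this is a drafting slip and nothing more. The list in 5.1.3 sits under the intervention heading and repeats the control list of 5.1.2 minus one item, "Retrospective VL testing on stored EDTA-derived plasma in case of clinical therapy failure", which the intervention arm does not need because its VLs are run in real time. So it is most naturally an edited list for the intervention arm, with the arm name left unchanged, and on that reading retrospective genotyping is planned in both arms. Section 5.2.6 contains no word that excludes the intervention arm. Table 4's silence proves little, since its resistance row is also blank for the control arm, where retrospective testing certainly is planned. Section 6.1 presupposes these genotypes. And persistent viraemia at the next visit triggers testing anyway.

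Most of this stands. A reader might infer that the protocol deliberately fixes selective genotyping by arm; the documents do not support that. They contradict each other. A reader might also infer that no control failure can lack a genotype. That is too strong as well: routine control VLs are taken at months 12 and 24, and 5.1.2 ties retrospective testing to therapy failure, so a control patient who is viraemic between those visits and resuppresses may never be identified.

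What does not fall away is the conflict with 5.2.6. Correcting the arm name in 5.1.3 leaves 5.2.6 naming one arm, and leaves clinical therapy failure untied to the no-drug pathway. Staff who work from 5.2.6 and 5.2.4.1 would leave those DBS untested. How to analyse failures without a sequence can be left to the SAP; whether the stored samples are tested is for the protocol to settle.

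**Conclusion.** The point holds as an internal contradiction with a real consequence if it is resolved the wrong way. Under 5.2.6 as written, a limited group of intervention failures has no planned genotype, and on the protocol's own expectation the missingness is informative. It affects mutations per failure, K65R or more than one NNRTI mutation, and averted switches.

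The size is unknown. With 10–30% ungenotyped, a K65R rate of 17% would appear somewhere between about 12% and 24%, with the direction set by how these patients are handled. If they are dropped and their K65R prevalence equals that of other failures, there is no shift.

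A reader might reach a larger figure from any-resistance rates. With 75% resistant overall, 30% ungenotyped and 30% resistance among those, dropping them gives 0.30 × (0.75 − 0.30) / 0.70 = 19 points. The last two inputs have no source in the documents. The result also implies (0.75 − 0.09) / 0.70 = 94% resistance among genotyped patients, above the 65–87% implied by section 2.1, where 13–35% of failures had no resistance mutations warranting a switch. That figure should not be used.

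**What to change.** 1. In 5.1.3, change control arm to intervention arm in the sample-collection paragraph.
2. In 5.2.6, extend retrospective genotyping on stored DBS to all patients in both arms who meet one virological failure definition (two consecutive VLs above 1000 copies/ml). State that this includes intervention patients whose DBS was not sent because no drug level was detected.
3. In 6.1, define the resistance outcomes, including averted switches, on that set in both arms.

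The added testing is done after the patient's follow-up and for outcome purposes only, so clinical management does not change. The cost is a small number of extra genotypes (about 5 to 15 on the illustrative shares) on DBS already stored, with no extra visit or blood draw. The change does not remove differences between the arms in how often viraemia is looked for; it ensures that identified failures are genotyped by the same rule.

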**Figure 1c: ITREMA study flowchart – follow-up of viremia in both arms**

[figure not shown]

Legend to flowcharts: **plasma**: EDTA-derived plasma, **DBS**: Dried Blood Spot, **PBMC**: Peripheral Blood Mononuclear Cell, **VL>1000**: Viral Load of 1000 copies/ml or more, **VL<1000**: Viral Load of less than 1000 copies/ml, **DLM**: Drug Level Measurement, **drug level +**: detectable concentrations of the NNRTI in plasma, **drug level -**: no detected NNRTI in plasma, **Resistance +**: Drug resistance mutations detected, **Resistance -**: No drug resistance mutations detected.

